## 1248 **REGULATORY REQUIREMENTS**

1249 The study will be authorised by the competent authority in each participating country.

1250 Enrolment of subjects will not start until approval has been received from both the Ethics  
1251 Committee(s) and Competent authorities.

1252 The study will be conducted in accordance with the Declaration of Helsinki, Good Clinical  
1253 Practice (GCP) and all other national requirements.

1254

## 1255 **INFORMED CONSENT**

1256 The statutory requirements for informed consent of participants in clinical trials of  
1257 investigational medicinal products (CTIMPs) are laid out in the European Clinical Trials  
1258 Directive (EC2001/20).  
1259

1260 Due to the nature of aSAH, it is expected that the majority of participants will be considered  
1261 to be ‘incapacitated adults’ at the time of entry into the study, where an incapacitated adult is  
1262 defined as “an adult unable by virtue of physical or mental incapacity to give informed  
1263 consent”. Overall the informed consent procedure shall not cause any delay in the treatment  
1264 or reduce the safety of the patients.

### 1265 *a. Informed Consent procedure in Austria:*

1266 The hierarchy for consent is considered to be:

|                                                                                                                                                                                                                                                                                                                                                                               |
|-------------------------------------------------------------------------------------------------------------------------------------------------------------------------------------------------------------------------------------------------------------------------------------------------------------------------------------------------------------------------------|
| 1. Patients with Capacity
Those patients able to give written informed consent                                                                                                                                                                                                                                                                                             |
| 2. Personal Legal Representative
A person not connected with the conduct of the trial who is:

(a) Suitable to act as the legal representative by virtue of their relationship with the adult,
and

(b) Available and willing to do so                                                                                                               |
| 3. No representative
In emergency situations where the treatment to be given to an incapacitated adult as part of the trial needs to be given urgently, time may not allow for the written consent of a legal representative to be obtained first.
Written informed consent will be obtained as soon as the participant is responsive or a representative is available. |

1267

1268 **Patients with capacity**

1269 Written and verbal versions of the patient information and informed consent form will be  
1270 presented to the participants detailing the exact nature of the trial, what it will involve for the  
1271 subject, the implications and constraints of the protocol and the known side effects and risks  
1272 involved in taking part. It will clearly state that the participant is free to withdraw from the  
1273 trial at any time for any reason without prejudice to future care and with no obligation to give  
1274 a reason for withdrawal.

1275 The patients will be allowed as much time as they need to decide whether to participate in the  
1276 trial. The 48-hour timeline for implantation will not be used to put pressure on the patient to  
1277 make a decision.

1278 The Investigator should explain to the patient that they are at liberty to refuse entry to the trial  
1279 or, should they decide to participate, to withdraw from the trial at any time. Such a decision  
1280 will not, in any way, affect their future management or treatment.

1281 Written informed consent will be obtained by means of participant dated signature with dated  
1282 signature of the person who presented and obtained the informed consent. The person who  
1283 obtains the consent must be suitably qualified and experienced and have been authorised to  
1284 do so by the Coordinating/Principal Investigator and the delegation log completed to  
1285 document this. A copy of the signed informed consent will be given to the participant and a  
1286 copy will be kept in the patient's notes. The original signed form will be retained in the  
1287 Investigator Site File (ISF).

1288 **Patients lacking capacity with Personal Legal Representative immediately available**

1289 Where patients lack capacity and the Personal Legal Representative is immediately available  
1290 in person, an identical approach will be taken substituting the Personal Legal Representative  
1291 for the patient.

1292 For patients that were unconscious at screening, and informed consent was obtained from  
1293 their Personal Legal Representative, written informed consent will be obtained and  
1294 documented from the patient as soon as they regain consciousness sufficiently to do so,  
1295 respecting their right to withdraw from the study should they wish to.

1296 The investigator will attempt to obtain consent until the completion of the study.

1297 Patients lacking capacity, with no personal legal representative may be recruited into the  
1298 study in emergency situations where the treatment to be given to an incapacitated adult as  
1299 part of the trial needs to be given urgently, time may not allow for the written consent of a  
1300 legal representative to be obtained first.

1301 Written consent will be obtained as soon as the participant is responsive or a representative is  
1302 available.

1303 ***b. Informed Consent procedure in Germany:***

1304 Patients lacking capacity may be recruited into the study if an independent physician, who is  
1305 not involved in the study and is able to assess the situation, confirms that the presumed will  
1306 of the patient has been determined and respected. The independent physician must not be part  
1307 of the study team and he has to be a medical specialist.

1308 **Determination procedure of the presumed will of the patient**

1309 Patients lacking capacity will only be included in this clinical trial if their participation is in  
1310 accordance with their presumed will. Patients' presumed will, will be, in general, to  
1311 participate in the clinical trial because they will have the chance to receive a potentially  
1312 superior treatment to the standard therapy. Patients not randomised to the treatment arm will  
1313 receive the standard therapy.

1314 The investigator will carefully check if patients have ever expressed that they are against  
1315 participating in clinical trials, even if the trial is in their best interest. To determine this, the  
1316 patient's companions, if available, will be consulted. Even if patients are only partially able  
1317 to follow the patient information because of aSAH's symptomatology, they are to be  
1318 informed and if they do not wish to participate in the clinical trial, they will not be included.

1319 The determination of the presumed will of the patient is the duty of the investigator. The  
1320 investigator must consider all known indications to determine the presumed will of the  
1321 patient. To prevent the investigator and the patient from wrong assessments, an independent  
1322 physician, who is not involved in the study, must be consulted.

1323 The procedure of determining the presumed will of the patient is to be documented. As soon  
1324 as the patient is sufficiently recovered, written informed consent will be obtained. If they  
1325 wish to withdraw from the study, their wishes will be respected.

1326 The investigator will attempt to obtain consent until the completion of the study.

1327

1328 **DIRECT ACCESS TO SOURCE DOCUMENTATION / DATA**

1329 The investigator must permit trial-related monitoring, audits by Sponsor, Sponsor  
1330 representative or regulatory authority, Ethics Committee review or regulatory inspection,  
1331 providing direct access to source data / documents.

1332 The CRF is defined as source data for rating scales i.e. Glasgow Coma Scale.

1333

1334 **STUDY MONITORING**

1335 It is understood that the study monitor(s) will contact and visit the investigator/clinical site  
1336 before the study, regularly throughout the study and after the study has been completed. At  
1337 these visits, the monitor(s) will inspect various study records; case report forms, investigator  
1338 site file and source data (patient records). No information in these records about the identity  
1339 of the subjects will leave the Trial site. The sponsor will maintain confidentiality of all  
1340 subject records. The investigator and / or site staff will be expected to be available if  
1341 requested by the monitor.

1342

1343 **QUALITY ASSURANCE**

1344 The sponsor (Brain Implant Therapeutics Pharma GmbH) or representative may perform an  
1345 audit at any time according to the sponsor's Standard Operating Procedure (SOP), in order to  
1346 verify whether the study is being conducted according to GCP.

1347

## 1348 **INSURANCE**

1349 Appropriate insurance cover has been undertaken in favour of patients participating in  
1350 clinical trials. The cover is provided to the patient on terms and conditions of the clinical trial  
1351 insurance. Insurance cover exists for health damages as a result of measures carried out in  
1352 connection with the clinical trial.

1353

## 1364 **PREMATURE TERMINATION OF THE STUDY**

1365 Both the sponsor and the investigator reserve the right to terminate the study at any time.  
1366 Should this be necessary, the procedures for an early termination or temporary halt will be  
1367 arranged after consultation with all parties.

1368

## 1369 **RECORD RETENTION**

1370 After completion of the study, all documents and data relating to the study will be kept in an  
1371 orderly manner by the Investigator in a secure study file.

1372 Essential documents must be retained for at least two years after the final marketing approval  
1373 in an ICH region or until two years have elapsed since the formal interruption of the clinical  
1374 development of the product under study.

1375 It is the responsibility of NeuroScios GmbH to inform the investigator of when these  
1376 documents can be destroyed. The Investigator must contact NeuroScios GmbH or the sponsor  
1377 before destroying any trial-related documentation. In addition, all subjects' medical records  
1378 and other source documentation will be kept for the maximum time permitted by the  
1379 institution.

1380

1381     **PUBLICATION OF RESULTS**

1382     The sponsor is entitled to publish and/or present any results at scientific meetings, and to  
1383     submit clinical trial data to national and international Regulatory Authorities. The sponsor  
1384     reserves the right to use such data for industrial purposes.

1385     Investigators must inform the sponsor before using the results of the study for publication or  
1386     conference and internal presentation and agree to provide the sponsor with a copy of the  
1387     proposed presentation.

1388

1389     **DATA SAFETY MONITORING BOARD (DSMB)**

1390     A committee will be set-up to monitor safety throughout the trial period. The committee will  
1391     comprise a group of at least three experts with the appropriate expertise - all of whom will be  
1392     independent of the sponsor and will not be involved in the conduct of the trial.

1393     A charter describing how the DSMB works and how it communicates with other study  
1394     participants (e.g. steering committee), will be prepared.

1395     The DSMB will review unblinded study information which will include:

- 1396             • List of any protocol violations  
1397             • Numbers of patient withdrawals/reason for withdrawal  
1398             • Adverse/serious adverse events  
1399             • Laboratory data

1400

1401     Following review of the safety data, the committee will prepare a written blinded report,  
1402     which will be forwarded to the steering committee and provide recommendations regarding  
1403     modifications, continuation or termination of the study.

1404     Where changes in the study conduct are recommended to the steering committee, sufficient  
1405     (blinded) information will be provided to allow the sponsor to decide whether and how to  
1406     implement these recommendations.

1407     **DSMB Meetings**

1408

1409     The DSMB will convene under the following circumstances:

- 1410             • 20 patients have been recruited and monitored to discharge or day 21, whichever  
1411             occurs first.
- 1412             • The DSMB must meet as soon as there has been a SUSAR.

1413

1414     In case of no SUSAR, the recruitment will continue throughout the DSMB meeting scheduled  
1415     after 20 patients. Specifically, the recruitment will continue also during the time the DSMB is  
1416     assessing the safety data in the initial 20 patients.

1417

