This procedure has already been successfully performed with a pharmaceutical equivalent known as nicardipine prolonged-release implants (NPRI) in over 250 aSAH patients. Up to 12 implants were used demonstrating excellent safety and tolerability profiles with no complications reported and no signs of neuronal toxicity or chemical meningitis [9, 10, 11, 12, 13]. All these studies demonstrated prevention of CV in vessels adjacent to the site(s) of implantation and decreased cerebral infarction and DIND. However, most of these studies lacked a control group.

NicaPlant® is a pharmaceutical equivalent of the NPRI; it has the same shape and size, same nicardipine free base load, similar excipient composition and comparable *in vitro* release profile.

In a recent phase IIa study the safety and tolerability of increasing doses (3, 6, 10 and 13 implants in 2, 2, 3 and 3 patients, respectively) was tested.

Eight serious adverse events occurred during the study that can be easily explained by the severe status of the patients and the major surgery. Five serious adverse events were classified as possible or probable related to the treatment either because of the lack of other explanations or, even if other explanations were more likely, a connection to the implants was still supposable. The variety of adverse events that can be suspected, already by developing a subarachnoid haemorrhage and the following clip ligation, and especially by reason of the small group a statistical evaluation of adverse reactions is not expedient.

The results of the phase IIa study overall demonstrate that NicaPlant® was safe and well tolerated. No obvious advantage from an exposure perspective could be observed with 13 versus 10 implants. More details of this study are presented in the Investigator's Brochure.

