## 340 **STUDY DESIGN**

### 341 **Overall study design and plan description**

342 This study is a randomised, single-blind, parallel-group design comparing 10 NicaPlant®  
343 implants / patient versus standard of care in overall 40 patients who have had aSAH.

344 The two groups of patients will be subjected to the following treatments:

- 345 • Standard of care plus NicaPlant®.
- 346 • Standard of care.

347 Both groups of patients will receive the standard of care according to treatment guidelines [8]  
348 and all further medical care will not be different between the groups. Patients in the  
349 interventional group will only in addition receive NicaPlant® implants.

350 NicaPlant® will be administered as per the implantation protocol, (in brief: by placement  
351 during microsurgical clipping of the ruptured aneurysm in proximity to all of the exposed  
352 cerebral blood vessels).

353 Patients will be assessed to determine the efficacy of NicaPlant® application to reduce the  
354 occurrence of angiographic cerebral vasospasm and to prevent early morbidity/mortality  
355 following aSAH. Cerebral vasospasm will be assessed by analysis of angiograms to  
356 determine narrowing of the proximal blood vessels.

357 Clinical Outcomes will be recorded at 12 weeks and 1 year (52 weeks) after the aSAH. Safety  
358 assessments will be made to confirm the safety and tolerability of the selected dose of  
359 NicaPlant®.

360 A data safety monitoring board (DSMB) will be set-up to monitor safety throughout the trial  
361 period and provide recommendations for any necessary actions. A steering committee will  
362 receive and review the blinded reports from the DSMB and take action as appropriate.

363 The DSMB will convene after 20 patients have been recruited and monitored to discharge, or  
364 day 21, whichever occurs earlier.

365 The final analysis will be carried out when the last patient completes the week 12 assessment,  
366 the database has been locked at this time point and unblinding has occurred. Data collected  
367 for patients at Week 52 after aSAH will be analysed and included as an addendum to the final  
368 report.

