#### 487 **Replacement of Withdrawn Patients**

488 Patients that withdraw prior to hospital discharge, or day 21, whichever occurs first, will be  
489 replaced. Replacement patients will receive the same treatment as the withdrawn patient. A  
490 maximum of 10 replacements will be done.

491 Patients who die will be considered to have completed the study and will not be replaced.

492

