#### 1085 **Power & Sample size**

1086 In order to ensure that the investigation of efficacy is adequately powered, the sample size  
1087 requirements are derived for the primary endpoint of interest.

1088 The primary endpoint is the Incidence of Cerebral Angiographic Vasospasm (Moderate to  
1089 Severe) at day 8 and these rates are compared for the active and control treatment groups  
1090 using the Fishers Exact test for differences in proportions. PASS software (Version 12; NCSS  
1091 LLC, Kaysville, UT, USA) was used for all calculations.

1092 A total of 40 patients (20 in each group) is in fact sufficient to detect a clinically relevant  
1093 difference of 50% between the active treatment and control group (active: 20%, control:  
1094 70%) with a two tailed significance level of 5% and 84% power.

1095 The Incidence rates from previous published work (Barth et al.,2007) were used as an  
1096 indicator of the likely incidence rates observed in a similar population with similar  
1097 investigations (Active: 7%, Control: 73%).

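### The DSMB is said to monitor safety throughout, but it has one scheduled meeting, after 20 patients, and then only a SUSAR convenes it; half the trial has no scheduled by-arm safety review

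*Protocol*

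**What the plan says.** **Scope.** Protocol section 23 (Data Safety Monitoring Board) states: "A committee will be set-up to monitor safety throughout the trial period". The Risks / benefits text in section 1 and the overall design description in section 3 say the same.

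**Meetings.** Section 3 gives the scheduled one: "The DSMB will convene after 20 patients have been recruited and monitored to discharge, or" day 21 if that is earlier. The DSMB Meetings list in section 23 repeats it and adds one event-driven occasion: "The DSMB must meet as soon as there has been a SUSAR". Recruitment is not paused for the scheduled review. The Interim Meetings paragraph provides for interim meetings on a SUSAR and on no other event.

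**What counts as a SUSAR.** Section 9 (Reporting serious adverse events to the sponsor) requires the event to be serious, unexpected and reasonably linked causally to the investigational product.

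**Stopping.** The Study Stopping Rules in section 23 rest on clinical judgement. One of the two asks whether adverse events on NicaPlant clearly exceed, in number or intensity, those seen under standard of care.

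**Who is blinded.** The table in section 6 lists the operating team as unblinded and the ICU team doing the safety assessments as blinded. Section 24 says that the executive committee is blinded, and section 23 has it receive a blinded report.

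**The concern.** The promise of monitoring throughout and the comparative stopping criterion both need the DSMB to see cumulative unblinded data from both arms as the trial proceeds. The list of meetings provides this once, at mid-recruitment. After that the only way back to the table is a trigger that looks at single events, one arm at a time, and filters them by causality and expectedness. It is not a comparison: control-arm events cannot be SUSARs, and a run of deaths or serious events on the implant that are each judged unrelated or expected convenes nobody.

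The implant cannot be withdrawn once placed, so protection of later patients depends on noticing an imbalance early. The executive committee that would act on it is blinded and relies on the DSMB's reports.

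**Working it through.** **1. The plan's own figure.** Section 11 says "A total of 40 patients (20 in each group) is in fact sufficient to detect a clinically relevant" "difference of 50% between the active treatment and control group (active: 20%, control" "70%) with a two tailed significance level of 5% and 84% power". Summing Bin(x; 20, 0.20) × Bin(y; 20, 0.70) over all tables where the two-sided Fisher p-value is at most 0.05 gives 84.6%, against 84% stated. The figure reproduces. It fixes 20 per arm as the base for the shares below and says nothing about safety monitoring.

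**2. Which events convene the DSMB after the first review.** Reading sections 9 and 23 together:

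| Event after the scheduled review | DSMB meeting? |
|---|---|
| Serious, related, unexpected, on NicaPlant | Yes (SUSAR) |
| Serious, related, expected, on NicaPlant | None provided |
| Serious or fatal, judged unrelated, on NicaPlant | None provided |
| Any event in the control arm | None provided |
| Growing imbalance between arms without a SUSAR | None provided |

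**3. Patients outside a scheduled review.** (40 − 20)/40 = 50%. Section 4 adds replacements ("Patients that withdraw prior to hospital discharge, or day 21, whichever occurs first, will be" replaced) with a maximum of 10, so at most (50 − 20)/50 = 60%.

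**4. How many serious events the SUSAR filter could miss.** Section 1 reports eight serious adverse events in 10 phase IIa patients, and "Five serious adverse events were classified as possible or probable related to the treatment". I read the five as part of the eight. As an assumption, apply that rate to the 10 NicaPlant patients of the second half: 10 × 8/10 = 8 serious events, of which 8 × 3/8 = 3 would not be classed as related and could not be SUSARs. Of the other 5, any judged expected would not qualify either. This counts events rather than patients, and it pools phase IIa doses of 3 to 13 implants.

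**5. What one review at 20 patients can show.** Assume an even split at each look and serious-event rates that are mine, not the protocol's. Power of a two-sided 5% Fisher comparison, by the same sum as in step 1:

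| Control v NicaPlant | 10 v 10 | 15 v 15 | 20 v 20 |
|---|---|---|---|
| 10% v 30% | 5.7% | 14.9% | 24.2% |
| 10% v 40% | 15.2% | 32.5% | 49.2% |

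The DSMB is not asked to run a significance test; the table only shows how little comparative information the single review holds.

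**6. What a look at 30 patients would add.** As a yardstick only, take an excess of at least 4 NicaPlant patients with a serious event. With D(n) = Bin(n, p on NicaPlant) − Bin(n, p on control), the chance that it is first seen at 30 patients is P(D(10) < 4 and D(15) ≥ 4).

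| Control v NicaPlant | Seen at 20 patients | First seen at 30 | First seen at 40 |
|---|---|---|---|
| 15% v 45% | 40% | 28% | 16% |
| 15% v 30% | 14% | 17% | 15% |
| 15% v 15% | 1% | 3% | 3% |
| 30% v 30% | 4% | 5% | 5% |

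The last column comes when all patients have been treated.

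**The case against.** The strongest reply is that the meeting list is a minimum. It does not say that no other meeting may be held, and section 23 leaves the board's working to a charter that is not shown and may add meetings. Nothing confines a SUSAR meeting to the index event, so one in the second half could review all accumulated data. This stands as a limit: how often the board would in fact meet is unknown. It does not remove the mismatch, because the protocol itself fixes the occasions and its list does not deliver what sections 1, 3 and 23 promise.

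A reader might infer more than the text supports:

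- **That serious events in the second half trigger nothing.** All serious adverse events go to pharmacovigilance within 24 hours whatever their causality and are passed to sponsor representatives. New adverse safety information must be reported to the DSMB, and safety reports are filed annually (section 9). The sponsor or the investigator may terminate the study at any time (section 20).
- **That nobody can see events by arm, so an imbalance surfaces only at the week 12 analysis.** The operating team is unblinded, and an imbalance could come to light earlier. What is missing is someone tasked to compare the arms cumulatively.
- **That the SUSAR trigger is empty because harms in this disease can be blamed on the haemorrhage or surgery.** Section 9 still grades an event as possibly related when concurrent disease could also explain it. Section 1 says that some phase IIa events were counted as related although other explanations were likelier. Many disease-like events could therefore still be SUSARs, and what is expected depends on the Investigator's Brochure, which is not shown.

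It is also fair that any simulated size of the gap depends on event rates and a threshold with no source in the documents, and that the board at 20 patients would use judgement, not a cutoff.

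**Conclusion.** The point holds as a mismatch within the protocol. Monitoring throughout and a comparative stopping criterion are stated, but one scheduled review and a SUSAR trigger are provided. Followed as written, 20 of 40 patients (up to 30 of 50) fall outside any scheduled by-arm safety review unless a SUSAR occurs.

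The trigger inventory and these shares rest on the protocol's text alone. The projection from phase IIa and the tables of assumed rates are illustrations. They suggest that the single review carries little comparative information and that a second look would add a useful amount, but the conclusion does not depend on them. The documents do not show that safety oversight lapses after 20 patients, nor do they support a numerical alarm tracked between reviews, which would need someone unblinded to follow the counts continuously. This is a cheap improvement, not a fatal flaw.

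**What to change.** Reconcile the DSMB Meetings and Interim Meetings text with the statements in sections 1, 3 and 23 and with the Study Stopping Rules. Add at least one further scheduled DSMB review in the second half to the meeting list, for example when 30 patients have reached discharge or day 21. The board would receive cumulative, unblinded counts of deaths and serious adverse events by arm, regardless of causality or expectedness, including later events in the first 20 patients. Make the matching change to the sentence in section 3.

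Keep the SUSAR meeting and the judgement-based stopping rules unchanged, and leave any numerical threshold to the DSMB charter.

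With a review at 30, the patients outside a scheduled review fall from 20 to 10 of 40 (25%), or to at most 20 of 50 (40%). The practical gain depends on recruitment speed, since enrolment continues while the 30th patient is followed.

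The cost is a protocol and charter sentence, one extra unblinded table and one meeting of the existing committee. There is a small chance of an unneeded discussion: about 3% to 5% at the extra review under the equal-rate rows above, if an excess of 4 were the prompt.
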